#### Statistical analysis

We developed a statistical analysis plan for our pragmatic RCT that includes sample size justification, descriptive statistics of our enrolled cohort, primary analysis on our primary outcomes, and supplementary secondary analyses on primary and secondary outcomes.

### Sample size justification

The sample size calculation was based on the primary analysis comparing the primary outcome (PEG scores) between the INSPIRE and control groups at 3 months. Based on the literature, we expect to observe an effect size of 0.3 in PEG score at 3 months [57, 58, 60, 70, 119, 120]. With a power of 0.8 and Type I error of 0.05 in a two-sided independent t-test, assuming 73% retention, a sample size of 586 (293/group) is needed at the enrollment to identify such an effect size at 3 months.

Although we will use Holm’s step-down procedure to adjust for multiple comparisons in secondary analyses, we will take a conservative approach in the power calculation for secondary analyses using Bonferroni with an individual Type I error of 0.01 to control for the family-wise Type I error in 5 comparisons on secondary outcomes. The sample size of 586 (293/group) at the enrollment will provide a power of 0.8 to detect an effect size of 0.366 (a group difference of 0.366*SD) in secondary outcomes between the INSPIRE and control groups. We consider the detectable effect sizes realistic that we expect to observe in the study. With a less conservative Holm’s step-down approach than Bonferroni that we will use in actual secondary analyses to adjust for multiple comparisons, the planned sample size will detect a smaller effect size than 0.366 with a power of 0.80 for secondary outcomes. Adverse events, severe adverse events, and unanticipated problems during the study will be summarized with frequencies and percentages and compared between the treatment groups using Fisher’s exact test or Chi-squared test as appropriate.

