#### Participant randomization

We will randomize at the level of the patient. While this poses a modest risk of provider contamination between intervention and control participants, providers will not receive any communication from the study team after enrollment. We have further addressed the potential effect of contamination by increasing sample size, allowing detection of smaller intervention effects.

Participants will be stratified by 4 demographic groups (Cantonese-speaking, Spanish-speaking, Black/African American English-speaking, and multi-cultural English-speaking) and randomly assigned 1:1 to either the INSPIRE intervention (Group 1) or control groups (Group 2). The CRC will utilize random block randomization to maximize balance between treatment groups throughout accrual while ensuring the randomization sequence remains unpredictable. A random allocation sequence was generated using a computer, where treatment groups were labeled as Group 1 or 2. After participants consent to study participation and complete baseline measures, clinical research coordinators will assign the next available study ID number in sequence, identify the allocated group, and inform participants of their assignment. The study ID number and Personal Health Information (PHI) will be stored in a HIPAA-compliant manner (REDCap) along with the intervention assignment (Group 1 or 2). Study personnel responsible for outcome evaluations will be blinded to which Group 1 or 2 represents.

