### Analysis of secondary endpoints

Secondary analyses will evaluate the ITT effects of the INSPIRE intervention on physical functioning, QOL, sleep, depression, anxiety, and global satisfaction with treatment with generalized linear mixed effects models (GLMM) like those used for the primary analysis. These GLMM will include language, time, treatment group, time*treatment in fixed effects while controlling correlations by clustering (clinics, providers, and participants). The time*treatment will assess if the secondary outcome changes over time differ by treatment groups. Holm’s step-down procedure will be used to adjust for multiple comparisons in secondary analyses [122].

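### The enrolment of 586 and the secondary detectable effect of 0.366 do not follow from the stated inputs; at 73% retention those inputs need about 482

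*Protocol article*

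**What the plan says.** All inputs for the primary calculation are in the protocol article, Sample size justification. The effect is given as "we expect to observe an effect size of 0.3 in PEG score at 3 months". The test is set out as "With a power of 0.8 and Type I error of 0.05 in a two-sided independent t-test". The result is "assuming 73% retention, a sample size of 586 (293/group) is needed at the enrollment to identify such an effect size at 3 months". Allocation is 1:1 (Participant randomization).

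For secondary outcomes the same section plans power by "using Bonferroni with an individual Type I error of 0.01 to control for the family-wise Type I error in 5 comparisons on secondary outcomes", and says that the 586 enrolled "will provide a power of 0.8 to detect an effect size of 0.366". The section names no design effect, no contamination factor and no second retention rate.

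Two other sections bear on the point. Participant randomization says: "We have further addressed the potential effect of contamination by increasing sample size, allowing detection of smaller intervention effects". It gives no figure. Analysis of secondary endpoints lists six outcomes: "physical functioning, QOL, sleep, depression, anxiety, and global satisfaction with treatment with generalized linear mixed effects models".

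**The concern.** The section gives every input that a two-group t-test calculation needs and then a result, so a reader can repeat it. The result comes out more than 100 participants above what the inputs require, which is too much for rounding or choice of formula.

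What is at stake is whether the justification can be relied on as a record. Effect size, power, retention, enrolment and the secondary detectable effect cannot all hold together as printed. Either the retention figure is not the one used, or a factor was applied and not reported, or the power and detectable effects are misreported. A reader who takes 73% at face value would understate the trial's power and overstate the smallest effects it can detect.

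**Working it through.** **Inputs** (protocol article, Sample size justification, unless noted): d = 0.3; two-sided alpha 0.05; power 0.80; independent t-test; retention 0.73; 1:1 allocation (Participant randomization); enrolment 293 per group; secondary alpha 0.01; secondary detectable effect 0.366.

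**1. Evaluable number per group, primary.**
- Normal approximation: n = 2(1.960 + 0.842)² / 0.3² = 174.4, so 175.
- Exact (noncentral t): n = 175.4, so 176.

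**2. Attempt to reproduce 586 at 73% retention.**
- 175.4 / 0.73 = 240.3, so 241 per group and 482 in total. Formula and rounding choices move the total only between 480 and 484.
- The printed total is 586. The difference is 586 − 482 = 104, or 104/482 = 22% above the requirement.
- Multiplying by 1.27 instead of dividing by 0.73 gives 446, which is further away.

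**3. Retention implied by 293 per group.**
- 176 / 293 = 0.601. Equivalently, 175.4 / 0.60 = 292.3, which rounds up to 293.

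**4. Secondary detectable effect (alpha 0.01, power 0.80, noncentral t).**
- At 73% retention: 293 × 0.73 = 213.9 per group, detectable effect 0.332.
- With no dropout (293 per group): 0.283.
- To obtain 0.366, 176.0 per group are needed, and 176.0 / 293 = 0.601.

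Both printed figures therefore rest on about 176 evaluable per group, not on 214.

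**5. Two routes to 176 per group.**
- Retention of 60%: 293 × 0.60 = 175.8, with detectable effects of 0.300 (alpha 0.05) and 0.366 (alpha 0.01).
- Retention of 73% with an extra factor: 213.9 / 175.4 = 1.22. Then 293 × 0.73 / 1.22 = 175.3, with detectable effects of 0.300 and 0.367.

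Within rounding, the printed figures cannot separate the two.

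**6. What 293 per group delivers.**

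| Retention, no other factor | Evaluable per group | Power for d = 0.3 | Detectable, alpha 0.05 | Detectable, alpha 0.01 |
|---|---|---|---|---|
| 73% | 214 | 0.87 | 0.27 | 0.33 |
| 60% | 176 | 0.80 | 0.30 | 0.366 |

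**7. Other readings tried.** Sidedness, alpha (0.05, 0.025, 0.01), power (0.80, 0.85, 0.90) and the inflation formula were varied. Only two kinds of variant come within 3% of 586:
- Two-sided alpha 0.025, divided by 0.73, gives 582.
- Power 0.90 with multiplication by 1.27 gives 596, at two-sided alpha 0.05 or its one-sided equivalent of 0.025.

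Each contradicts a stated input, and neither gives 0.366 at 73% retention.

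**8. Number of comparisons.** 0.05/5 = 0.01, as printed. With six comparisons, alpha is 0.05/6 = 0.0083, and the detectable effect is 0.373 at 176 per group or 0.338 at 214 per group.

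**The case against.** The best defence is that the surplus is deliberate. Participant randomization says the sample was enlarged because of contamination, and the primary model allows for clustering by clinic and provider. A factor of about 1.22 on top of 73% retention would reproduce both printed figures. This stands to the following extent: a reader might infer from the match at 60% that the calculation used 60% and that 73% is an error, and the document does not support that inference. The two figures fix only the effective number per group. The defence does not rescue the text, though. No factor is given anywhere, and the justification presents 586 as the number required for 0.3 itself under a plain t-test at 3 months.

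A second objection is that the error is on the safe side. That is correct. Under either reading the trial has at least its stated power for 0.3.

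A reader might also infer that a 60% assumption would weaken the missing-at-random primary analysis. That goes too far. How far the model can be trusted depends on the missingness actually observed and its mechanism, and Secondary analyses of the primary outcome already plans dropout-covariate checks, multiple imputation and pattern mixture models.

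On five against six comparisons, the count of six is not clearly the right one. Sleep is measured by more than one instrument, and Global Impression of Change has no baseline value in Table 1, so five may count the domains measured at baseline. The document does not say.

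**Conclusion.** The point holds as an arithmetic inconsistency. With the printed inputs the requirement is about 482 (480 to 484), not 586, and the secondary detectable effect at 73% retention is 0.33, not 0.366. Both printed figures imply about 176 evaluable per group. Whether that reflects about 60% retention, or 73% with an unreported factor of about 1.22, cannot be settled from the document.

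It is not a power shortfall: power for 0.3 is about 0.87 at 73% and 0.80 at 60%. The result assumes a standardised effect, equal groups, the t-test named in the plan, and dropout handled by dividing by the retention rate. The comparison count is a minor matter, moving the detectable effect from 0.366 to 0.373 at 176 per group.

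**What to change.** Keep the enrolment at 586 and correct Sample size justification in one of three ways, according to what was actually done:

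- (a) If about 60% retention was assumed, state it in place of 73%; 586, power 0.8 and 0.366 then stand.
- (b) If 73% is the assumption and no other factor was used, keep it and restate power as about 0.87 for an effect of 0.3, with detectable effects of about 0.27 (primary) and 0.33 (secondary, alpha 0.01).
- (c) If the sample was inflated for contamination or another reason, state the factor (about 1.22) and its basis, and make this section agree with Participant randomization.

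Also state which comparisons form the secondary family. If there are six, give the detectable effect as about 0.373 at 176 per group or 0.338 at 214 per group.

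The cost is wording and a few recomputed figures. Enrolment and the analysis do not change.

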**Methods:**

The Integrating Nonpharmacologic Strategies for Pain with Inclusion, Respect, and Equity (INSPIRE) study evaluates a blend of these non-pharmacologic, evidence-based interventions using a pragmatic, parallel, two-arm RCT comparing intervention participants with wait-list controls. The INSPIRE intervention includes a 12-week curriculum delivered via a multilingual mobile app paired with weekly telehealth coaching. The primary outcome will be the “Pain, Enjoyment, and General Activity (PEG)” scores at 3 months. Secondary outcomes include PEG scores at 6 and 12 months, physical functioning, quality of life, sleep, depression, anxiety, and global satisfaction with treatment at 3, 6, and 12 months. Primary mediators to be examined include pain cognitions and health behaviors. Secondary mediators may include stigma and isolation, trust in healthcare providers, and both engagement and satisfaction with the INSPIRE intervention. The intention-to-treat primary analysis will be conducted with covariates including baseline measures of pain, anxiety, and physical function.

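### The secondary power statement counts five comparisons, but the analysis section puts six named outcomes under Holm, so the stated 0.01 level and 0.366 detectable effect belong to a different family

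*Protocol article*

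**What the plan says.** All references are to the protocol article.

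- **Sample size justification** sets the secondary level by Bonferroni: "individual Type I error of 0.01 to control for the family-wise Type I error in 5 comparisons on secondary outcomes". It continues: "The sample size of 586 (293/group) at the enrollment will provide a power of 0.8 to detect an effect size of 0.366". The five comparisons are not named.
- The same section calls this conservative, because the analysis itself will use Holm, and concludes that "the planned sample size will detect a smaller effect size than 0.366 with a power of 0.80 for secondary outcomes".
- Its first paragraph gives the primary inputs: "we expect to observe an effect size of 0.3 in PEG score at 3 months", and "With a power of 0.8 and Type I error of 0.05 in a two-sided independent t-test, assuming 73% retention".
- **Analysis of secondary endpoints** names six outcomes for the Holm-adjusted analysis: "physical functioning, QOL, sleep, depression, anxiety, and global satisfaction with treatment with generalized linear mixed effects models (GLMM"). It describes one group-by-time assessment per outcome.
- The **Abstract** (Methods) lists the same six: "physical functioning, quality of life, sleep, depression, anxiety, and global satisfaction with treatment at 3, 6, and 12 months". The **Secondary outcomes** section also lists them separately.

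**The concern.** A Bonferroni level is the family-wise level divided by the number of tests, and Holm's first step uses the same divisor. If the power statement divides by five and the analysis tests six, then the stated level, detectable effect and power are not those of the planned analysis. Holm's first threshold for six outcomes is also stricter than the 0.01 that the article presents as the conservative choice.

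Two things are at stake. The first is whether a stated figure is correct. The second is whether the family is fixed in advance: Holm's thresholds depend on how many hypotheses are counted, and the article supports more than one count.

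**Working it through.** **1. Can the count be five?** Only the Trial design section comes close, because it joins physical functioning and quality of life with a slash. Table 1 gives these two different instruments (PROMIS Physical functioning 6b and WHOQOL) and different follow-up visits (3, 6 and 12 months against 12 months only). The analysis section lists them separately. PEG at 6 and 12 months does not explain the five either: Secondary analyses of the primary outcome tests it at an unadjusted 0.05.

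Six may be too low. The Secondary outcomes section names two PROMIS sleep forms, and Table 1 also places sleep duration and TAPS under secondary outcomes.

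**2. Inputs.** Two-sided independent t-test, power 0.80, allocation 1:1, 293 enrolled per group and 73% retention, all from the article. Family-wise level 0.05, which is implied by 5 × 0.01.

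**3. Formula.** The detectable standardised difference with n analysed per group is approximately

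d = (z(1 − α/2) + z(0.80)) × √(2/n).

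The results below use the exact noncentral t, which gives slightly larger values.

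**4. Reproducing the article's figure.**

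- Level: 0.05/5 = 0.01, as stated.
- At the stated retention, n = 293 × 0.73 = 213.9, or 214. The normal approximation gives (2.576 + 0.842) × √(2/214) = 0.330 and the exact t gives 0.332. This is not 0.366.
- With n = 176, the approximation gives (2.576 + 0.842) × √(2/176) = 0.364 and the exact t gives 0.366, with power 0.800. This reproduces the stated figure.
- 176 per group is also what a t-test needs for 0.3 SD at α = 0.05 and power 0.80. It is 176/293 = 60% of enrolment, not 73%. That 60% was used is inferred from the arithmetic; the article does not say so.

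**5. Six comparisons.** α = 0.05/6 = 0.00833, with z = 2.638. The normal approximation gives (2.638 + 0.842) × √(2/176) = 0.371 and (2.638 + 0.842) × √(2/214) = 0.336. Exact t results:

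| Analysed per group | Comparisons | α per test | Detectable d | Power at 0.366 |
|---|---|---|---|---|
| 176 | 5 | 0.0100 | 0.366 | 0.80 |
| 176 | 6 | 0.0083 | 0.373 | 0.78 |
| 214 | 5 | 0.0100 | 0.332 | 0.88 |
| 214 | 6 | 0.0083 | 0.338 | 0.87 |

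Moving from five to six costs 0.373 − 0.366 = 0.007 SD at 176 per group, or 0.338 − 0.332 = 0.006 SD at 214.

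**6. The Holm sentence.** I simulated Holm on six outcomes with pairwise correlation 0.5 (an assumption) and d = 0.366 for each outcome with a true effect. At 176 per group, power for one such outcome is about 0.79 if it is the only one with an effect, 0.80 if two have one, 0.81 if three do, and 0.87 if all six do. At 214 per group it is about 0.87 even with one. So, at the number behind 0.366, the claim that Holm detects less than 0.366 with power 0.80 depends on how many outcomes respond. At the stated retention it holds for six outcomes.

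**The case against.** The strongest reply is that nothing breaks. Under the article's own 73% retention, six comparisons leave power of 0.87 at 0.366, and power there stays at or above 0.80 for up to 14 comparisons (0.803 at 14, 0.797 at 15). Enrolment is set by the primary outcome. For a given family, Holm is indeed less conservative than Bonferroni, and detailed family membership is commonly left to the analysis plan. All of this stands, and it keeps the point small. It does not remove it: the article itself prints a count, a level and a detectable effect, and its own analysis section contradicts the count.

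Two stronger readings are tempting, and the document supports neither.

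- **Six outcomes at three visits make up to 18 tests.** The Abstract and Trial design attach 3, 6 and 12 months to the outcomes, but as assessment times. The analysis section describes one group-by-time assessment per outcome. Table 1 also has QOL at 12 months only and Global Impression of Change at 3 and 12 months, so not every outcome has three follow-up visits.
- **The family-wise error rate is inflated.** This would need a fixed 0.01 to be applied to each test of a larger family. The article uses 0.01 only in the power calculation. Holm, applied to the family actually tested, controls the error rate whatever the power statement counted.

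**Conclusion.** The inconsistency is real and minor. The power statement assumes five unnamed comparisons; the analysis names six. The level for six is 0.0083, and the detectable effect at 80% power is 0.373 with 176 analysed per group or 0.338 with 214, so 0.366 is right for neither. These figures assume a two-sided t-test, as in the article, and exactly six tests. More than one sleep measure, or TAPS, in the family would lower the level further.

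The larger numerical gap is that 0.366 fits about 60% retention and not the stated 73%. That is a separate matter, but any restated figure has to settle it.

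**What to change.** - In Sample size justification, replace five and 0.01 with six and 0.0083, or with the actual count and level if more than one sleep measure or TAPS belongs to the family.
- Restate the detectable effect at an analysed number consistent with the stated retention: 0.338 SD for six outcomes at 73% (214 per group). If 176 analysed per group is what was meant, state that retention and give 0.373.
- Replace the sentence on Holm and 0.366 with a statement that Holm has at least the power of Bonferroni for the same family.
- In Analysis of secondary endpoints, list each outcome in the Holm family with its instrument and its single contrast. Which contrast is the sponsor's choice.

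The cost is a wording change made before the analysis. It needs no extra participants or data, and neither enrolment nor the testing procedure changes.

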### General statistical considerations

Participants’ demographic characteristics (i.e., age, sex, race/ethnicity, socioeconomic status, marriage status) and clinical characteristics at baseline and follow-up will be summarized by intervention groups (INSPIRE vs. control) as well as by sex and language groups to assess potential differences in sex and language groups. Boxplots and other appropriate plots will be used to assess the balance of baseline characteristics between the two groups. The distributions of outcome measures will be checked by histograms and other appropriate plots for the selection of appropriate analysis methods and potential data transformation. Graphs of outcomes over time will be used to determine an appropriate way to model the time effect.

### Primary analysis of the primary endpoint

Our primary analyses will assess the intention-to-treat (ITT) effect of INSPIRE on PEG score compared to the control group at 3 months. The ITT approach will include all the randomized participants, including non-adherers and dropouts, in the analyses. A linear mixed effects model (LMM) will evaluate the group difference over time in change in PEG scores. The models will include the stratification variable (language), group (INSPIRE vs. control), time, and time*group interaction as fixed effects, and random intercept and slope for the nested three-level random effects controlling for correlation due to clustering by clinics, providers, and participants. Baseline demographics and characteristics will be balanced between the two groups by randomization; if any baseline covariates are identified as imbalanced, these will also be included in models. Time will be included in the LMM in an appropriate way (linear, categorical, quadratic, or two pieces) based on the graph of the outcome over time. The time*group interaction will provide the estimated ITT effect of INSPIRE compared to control over time, where the contrast between the INSPIRE and control groups at 3 months is our primary interest, using a significance level of 0.05. The LMM adopts a less stringent assumption on missingness (i.e., missing at random) than complete case approaches (missing completely at random) and will include all available data from all the randomized participants in the analysis.

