#### Objective

We developed a culturally tailored, trilingual mobile phone app that blends CBT, MBI, and MFI delivered over 12 weekly modules and supported by weekly health coaching to address non-malignant chronic pain in adult primary care patients. This Phase III clinical trial will assess the effectiveness of this intervention and examine potential mediators. We hypothesize that INSPIRE participants will show significantly greater reductions in PEG scores (i.e., pain intensity, interference of enjoyment, and reductions in general activities) from baseline to 3 months (i.e., primary outcome) in comparison to waitlist controls with additional assessments at 6 and 12 months. Secondary outcomes will include the HEAL CDE measures and analysis of potential primary mediators (e.g., catastrophizing, self-efficacy, psychological flexibility) and secondary mediators (e.g., trust, lower stigma).

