## Methods

### Trial design

The efficacy of the INSPIRE intervention will be determined by a multisite, parallel, two-arm pragmatic RCT comparing intervention participants with waitlist controls over a study period of 12 months. The primary outcome will be PEG scores at 3 months with secondary outcomes including PEG at 6 and 12 months, and physical functioning/quality of life, sleep, depression, anxiety, and global satisfaction with treatment at 3, 6, and 12 months. Secondary analyses will also determine if primary mediators of pain cognitions (catastrophizing, psychological flexibility, pain self-efficacy) and health behavior (behavioral activation, exercise, movement) and secondary mediators of stigma and isolation, trust in healthcare, and satisfaction with the INSPIRE intervention play a role in improved pain outcomes.

The feasibility and acceptance (F&A) of this research protocol was first assessed in a 3-month, single-arm pilot of *n*=24 participants (8 from each language group). F&A outcomes included the success of participant recruitment and retention, patient adherence, intervention fidelity, data collection tools and schedule, and participant satisfaction. Feedback on the trial methodology and the mobile app was collected and used for optimization prior to the start of the RCT. The study protocol is summarized in the flowchart (Fig. 1). The Study protocol adheres to the Standard Protocol Items: Recommendations for Interventional Trials (SPIRIT) 2025 guidelines [79]. The SPIRIT Checklist can be found in Additional file 2, and the “SPIRIT Figure” study timeline can be found in Table 1.

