### Primary outcome

The primary outcome will be Pain, Enjoyment, and General Activity (PEG) score at 3 months. The PEG is a validated 3-item pain assessment tool measuring self-reported pain intensity (P) and interference with enjoyment (E) and general activities (G); items are rated 0–10, with the final PEG score averaging responses over 3 items, with a range of 0–10 [80, 117]. Higher values correspond to worse pain experience and interference.

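### The primary PEG comparison is given both as a 3-month level and as a change from baseline, and the primary model does not settle which is tested or how baseline PEG enters

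*Protocol article*

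**What the plan says.** **Level.** The Primary outcome section states: "The primary outcome will be Pain, Enjoyment, and General Activity (PEG) score at 3 months". Trial design agrees ("The primary outcome will be PEG scores at 3 months"), as does the Abstract. The Sample size justification bases the calculation on an independent t-test "comparing the primary outcome (PEG scores) between the INSPIRE and control groups at 3 months".

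**Change.** The Objective hypothesizes that INSPIRE participants "will show significantly greater reductions in PEG scores", and continues "from baseline to 3 months (i.e., primary outcome) in comparison to waitlist controls". As written, the label falls on a reduction from baseline.

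**Model.** The section on the primary analysis of the primary endpoint opens with PEG at 3 months, then says "A linear mixed effects model (LMM) will evaluate the group difference over time in change in PEG scores". The fixed effects are language, group, time and time-by-group. One sentence says that the interaction gives the intention-to-treat effect and also refers to the contrast: "where the contrast between the INSPIRE and control groups at 3 months is our primary interest". Baseline PEG is not listed as a covariate; a baseline variable enters only if found imbalanced. The Abstract, by contrast, says that the primary analysis has baseline pain among its covariates. The secondary analyses of PEG describe the 6- and 12-month contrasts from the same model as differences in PEG score.

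**The concern.** In a model with baseline PEG among the responses, categorical time and a free group term, the interaction at 3 months is the between-group difference in change. The group contrast at 3 months is the group term plus that interaction, which is the difference in level. The two differ by the estimated baseline difference between arms. With baseline PEG as a covariate, as in the Abstract, that distinction disappears, but the model in the analysis section does not contain it.

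The article therefore supports more than one analysis for its only confirmatory test. At stake are which p-value is reported as primary, what power it has, and whether the choice could be made after both results are known.

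**Working it through.** **The plan's own figure.** For d = 0.3, two-sided alpha 0.05 and power 0.80, n per group = 2 × (1.960 + 0.842)² / 0.3² ≈ 175, or 176 with the t distribution. At 73% retention, 176 / 0.73 gives 242 per group, 484 in total, not the stated 586. The stated 293 per group corresponds to 176 / 293 = 60% retention. That mismatch is a separate matter and does not bear on this point. The check below uses the stated enrolment and retention: 293 randomized and 293 × 0.73 ≈ 214 observed at 3 months per arm.

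**Assumptions.** The document gives no PEG standard deviation and no baseline to 3-month correlation r. I use SD = 1 at both times, a true difference of 0.3 SD at 3 months, and r = 0.3, 0.5 and 0.7. The model is reduced to two time points with categorical time. Later visits and clustering by clinic and provider are left out.

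**Variances per arm**, with all 293 baseline values and 214 values at 3 months:

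- Level: V_L = (1 − r²)/214 + r²/293
- Change: V_C = V_L + 1/293 − 2r/293
- Baseline-adjusted: V_A = (1 − r²)/214
- SE of the group difference = √(2V); power = Φ(0.3/SE − 1.96)

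Example at r = 0.3: V_L = 0.91/214 + 0.09/293 = 0.00456, SE 0.0955, power Φ(3.14 − 1.96) = 0.88. V_C = 0.00456 + 0.4/293 = 0.00592, SE 0.109, power Φ(2.75 − 1.96) = 0.79.

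| r | SE level | SE change | SE adjusted | Power level | Power change | Power adjusted |
|---|---|---|---|---|---|---|
| 0.3 | 0.0955 | 0.1089 | 0.0922 | 0.881 | 0.787 | 0.902 |
| 0.5 | 0.0934 | 0.0934 | 0.0837 | 0.895 | 0.895 | 0.948 |
| 0.7 | 0.0901 | 0.0734 | 0.0690 | 0.915 | 0.983 | 0.991 |

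**Disagreement between the tests.** The correlation of the two test statistics is (V_L − r/293)/√(V_L V_C) = 0.68, 0.61 and 0.51. Simulating pairs of statistics with these correlations gives:

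| r | Disagree on significance, true effect 0.3 SD | Either significant, no true effect |
|---|---|---|
| 0.3 | 17% | 8.4% |
| 0.5 | 12% | 8.7% |
| 0.7 | 9% | 9.0% |

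**One data set, two answers.** The chance baseline difference has SE √(2/293) = 0.083 SD, so 0.1 SD is unremarkable. Take r = 0.5 and an observed 3-month advantage of 0.25 SD for INSPIRE. On the level, z = 0.25/0.0934 = 2.68, p = 0.007. If INSPIRE started 0.1 SD better, the change difference is 0.15, z = 1.61, p = 0.11. If it started 0.1 SD worse, the change difference is 0.35, z = 3.75, p = 0.0002.

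**The case against.** The formal definitions agree: Abstract, Trial design, Primary outcome and Sample size justification all give PEG at 3 months. The Objective's label directly follows the words for the 3-month time and may mark only the time point, against the 6- and 12-month assessments. The interaction sentence can be read as one quantity, the interaction's contrast at 3 months. Detail on the contrast and on baseline handling is often left to the analysis plan, which exists but is not shown, and analysts are blinded to condition.

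Much of this narrows the point without removing it. The single-quantity reading is a difference in change, which still does not match the level definition. The article goes beyond leaving detail to the analysis plan: it states the model terms, the effect and the alpha, and an analysis plan cannot agree with all of these statements. Blinding to group labels does not hide which of two two-sided p-values is smaller.

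Three stronger readings are tempting and are not supported:

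- A reader might infer that the response is literally a change score, so that participants without follow-up drop out despite the intention-to-treat statement. The wording about change is ordinary shorthand for an interaction. The random intercepts and slopes and the use of all available data point to repeated PEG scores as the response.
- A reader might infer that power could fall well below 80%. That needs 176 analysed per group and completer t-tests. With the stated 73% retention and a mixed model, the lowest value over the assumed correlations is 0.79.
- A reader might infer two different treatment effects. Randomization gives both quantities the same expected value.

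**Conclusion.** The point holds as a defect of specification: the primary estimator and p-value are not fixed, and the Abstract and the analysis section disagree on baseline adjustment. Each test on its own is valid at 5%. The inflation to about 8–9% arises only if the more favourable result is chosen after both are seen, and nothing in the document says that this is intended.

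The consequence is moderate: disagreement on significance in roughly one trial in six to one in eleven at the planned effect, and interaction power between 0.79 and 0.98 against 0.88 to 0.92 for the level. Power is equal at r = 0.5. These figures rest on the assumed correlations, equal SDs, 73% retention and a two-time-point simplification. They also read the planned 0.3 as scaled by the SD of the 3-month score, which the document does not say. That the two contrasts differ under the listed model does not depend on those values.

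**What to change.** State one primary quantity, the between-group difference in mean PEG at 3 months, in the Abstract, Objective, Primary outcome, Sample size justification and primary analysis sections. In the Objective, attach the primary label to that quantity. In the primary analysis section, remove the reference to change and name the single contrast tested at 0.05.

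Say how baseline PEG enters, in one of two ways:

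- as a response, with a common baseline mean for both arms (no group difference at baseline, group-by-time terms after it), which keeps participants who have only a baseline value in the model; or
- as a covariate, with only follow-up scores as responses, as the Abstract already indicates.

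Make the Abstract and the analysis section agree on the choice. Under either option the level and change contrasts at 3 months coincide, and power is about 0.90, 0.95 and 0.99 at correlations of 0.3, 0.5 and 0.7.

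The cost is a few wording changes and one model line. Baseline PEG is already collected, and no patients are added. It should be settled before outcome data are examined by arm.
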